### Statistical Methods

The primary analysis for this trial will be based on the intention-to-treat principle and will include all randomized patients, with treatment effects based on the assigned treatment regardless of the treatment they received and whether they completed the trial.

#### Primary Outcome Analysis

The primary outcome, time to clinical stabilization, will be analyzed using a Cox proportional hazard regression model with treatment group as the primary exposure. Results will be reported as hazard ratios with 95% CIs accounting for censoring. The proportional hazard assumption will be assessed using Schoenfeld residuals and log-log survival plots.

The primary Cox model will be adjusted for the following prespecified baseline covariates selected a priori based on clinical relevance: age, sex, baseline pneumonia severity (confusion, uremia, respiratory rate, blood pressure, and age ≥65 years [CURB-65] score), baseline C-reactive protein concentration, and key comorbidities (eg, chronic cardiovascular, respiratory, or metabolic conditions). These covariates were selected to account for potential confounding effects of multimorbidity on clinical recovery. Randomization is stratified by pneumonia severity to ensure balance between groups across this critical prognostic variable.

As a sensitivity analysis, time to clinical stabilization will also be assessed using restricted mean survival time over a clinically relevant time horizon, providing an absolute measure of treatment effect that does not rely on the proportional hazard assumption.

An additional sensitivity analysis will be performed using an independent-sample *t* test (2-sided) or linear regression depending on the distribution of the outcome. The linear regression model will allow for adjustment for the same prespecified covariates, and results will be reported as mean differences with 95% CIs.

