## Methods

### Study Design

This study is a single-center, double-blind, placebo-controlled, parallel-group randomized clinical trial designed in accordance with the SPIRIT (Standard Protocol Items: Recommendations for Interventional Trials) 2013 statement. Participants will be randomly allocated in a 1:1 ratio to receive either high-dose oral vitamin C (as sodium ascorbate) or a matching placebo in addition to standard care for CAP (Figure 1).

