### Sample Size Calculation

The sample size was based on a previous RCT [16], which reported that the mean time to clinical stabilization (used as a proxy for hospital discharge) in patients with CAP was 3.6 (SD 1.9) days in patients who were in the vitamin C group compared to 4.7 (SD 2.0) days in the placebo group. Using this effect size (1.1 days), a pooled SD of 1.95, a power of 80%, and a 2-sided α of .05, the required sample size is 102 participants (51 per group). To account for an anticipated 20% attrition rate due to loss to follow-up or mortality, we plan to recruit 124 participants (62 per group).

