### Data Collection and Follow-Up

Clinical data will be collected daily during hospitalization. Follow-up assessments will be conducted at 30 days and 6 months after randomization via telephone interview. Data will be recorded using secure electronic case report forms. The schedule of enrollment, interventions, and outcome assessments is summarized in Table 1.

**Table 1 table1:** Schedule of enrollment, interventions, and assessments for the Vitamin C in Community-Acquired Pneumonia trial.

	Screening and baseline	Day 0—randomization	Days 1-7—hospital phase	Day 30—follow-up	Month 6—follow-up
Eligibility assessment	✓				
Informed consent	✓				
Randomization		✓			
Vitamin C or placebo administration		✓	✓	✓	
Clinical observations (vital signs)	✓	✓	✓^a^		
CAP^b^ symptom assessment	✓		✓	✓	
Early clinical response assessment			✓^c^		
Inflammatory biomarkers (CRP^d^ and PCT^e^)	✓		✓^f^		
Hospital outcomes (ICU^g^ admission, ventilation, and vasopressor use)			✓		
Length of stay			✓		
Adverse event monitoring		✓	✓	✓	✓
Hospital readmission				✓	
Health-related quality of life (EQ-5D-5L)				✓	✓
Mortality assessment			✓	✓	✓

^a^Daily during hospitalization (days 1-7).

^b^CAP: community-acquired pneumonia.

^c^Assessed on days 3-5.

^d^CRP: C-reactive protein.

^e^PCT: procalcitonin.

^f^Measured on day 7 or at discharge (whichever occurs first).

^g^ICU: intensive care unit.

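### The primary Cox model has no term for how far a patient is from the endpoint at randomization: a cheap efficiency gain forgone, not an error

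*Protocol article*

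**What the plan says.** Textbox 2 makes the primary event a joint one: temperature, heart rate, respiratory rate, systolic blood pressure and oxygenation must all satisfy their limits. The Outcomes section starts the clock at randomization.

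Primary Outcome Analysis specifies a Cox model adjusted for "age, sex, baseline pneumonia severity (confusion, uremia, respiratory rate, blood pressure, and age ≥65 years [CURB-65] score), baseline C-reactive protein concentration" and key comorbidities, all chosen in advance. The same covariates serve the adjusted linear-regression sensitivity analysis. Randomization is stratified by pneumonia severity.

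Table 1, under Data Collection and Follow-Up, has a row "Clinical observations (vital signs" that is ticked at screening and baseline, on day 0 and on days 1 to 7. It does not list the individual signs.

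The eligibility criteria allow randomization up to 48 hours after admission. None of them requires a patient to be failing any of the five criteria at entry.

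The sample size compares two means: "Using this effect size (1.1 days), a pooled SD of 1.95", with "a power of 80%, and a 2-sided α of .05", and "the required sample size is 102 participants (51 per group".

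**The concern.** For an endpoint defined by crossing thresholds, the starting position is the natural baseline value of the outcome. A patient failing one criterion at randomization will plausibly stabilize sooner than one failing four. With entry allowed anywhere in a 48-hour window and no instability requirement, starting positions may differ widely.

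The covariate list has nothing that measures this directly. CURB-65 is a partial stand-in: it carries respiratory rate and blood pressure as score items, alongside confusion, urea and age, but not temperature, heart rate or oxygenation.

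The list is stated as prespecified for the primary model, so an analysis plan that follows it would carry the gap forward. At stake is precision in a small trial. In a Cox model, leaving out a prognostic covariate also pulls the hazard ratio toward 1 relative to the conditional one.

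**Working it through.** **Coverage of the endpoint by the planned covariates**

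| Textbox 2 criterion | In a planned covariate? |
|---|---|
| Temperature | No |
| Heart rate | No |
| Respiratory rate | Only as a CURB-65 item |
| Systolic blood pressure | Only through the CURB-65 blood-pressure item |
| Oxygenation | No |

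Three of five are absent and two enter in part. Baseline CRP and age may be correlated with starting status but do not measure it.

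**The plan's own figure.** Inputs from Sample Size Calculation: difference 1.1 days, SD 1.95, two-sided alpha 0.05, power 80%, 1:1 allocation.

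Normal approximation: n per group = 2 × (1.960 + 0.842)² × (1.95/1.1)² = 49.3, so 50. The two-sample t version gives 50.3, so 51 per group and 102 in total. The stated figure is reproduced. Power at 51 per group is 80.5%. No covariate enters this calculation.

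**Gain from one more prognostic term (linear model).** Assume that the planned covariates together correlate 0.3 with the outcome, and let r be the partial correlation of starting status given those covariates. Neither value is in the documents. Then:

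residual SD = 1.95 × √(1 − 0.3²) × √(1 − r²)

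With the planned covariates alone (r = 0) this is 1.95 × √0.91 = 1.860. The standardized effect is 1.1/1.860 = 0.591, and power at 51 per group is 84.1%.

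| r | Residual SD | 1.1 / SD | Power | Gain (points) |
|---|---|---|---|---|
| 0 | 1.860 | 0.591 | 84.1% | 0 |
| 0.2 | 1.823 | 0.604 | 85.5% | 1.4 |
| 0.3 | 1.774 | 0.620 | 87.3% | 3.2 |
| 0.4 | 1.705 | 0.645 | 89.7% | 5.6 |
| 0.5 | 1.611 | 0.683 | 92.7% | 8.6 |

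The right baseline is 84.1%, not 80.5%, because the planned model already adjusts for several covariates.

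**Does the Cox model behave similarly?** Two simulations were run, both on assumed prognostic strengths.

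- Gamma-distributed times with the plan's means (3.6 and 4.7 days) and SDs (1.9 and 2.0), whole-day readings, no censoring, a planned-covariate score at correlation 0.3, and size-adjusted critical values:

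| Per group | Partial correlation | Without term | With term | Gain (points) |
|---|---|---|---|---|
| 50 | 0.3 | 69.6% | 73.7% | 4.1 |
| 50 | 0.5 | 70.2% | 79.5% | 9.3 |
| 62 | 0.3 | 76.3% | 78.9% | 2.6 |
| 62 | 0.5 | 77.6% | 86.5% | 8.9 |

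  With 1,500 replicates, each power has a Monte Carlo standard error of about √(0.77 × 0.23/1500) = 1.1 points.

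- Exponential times, 99 events, an assumed conditional hazard ratio of 1.77, and respiratory rate and blood pressure partly captured by a CURB-65 proxy. The spread is the SD of the log hazard carried by the five signs:

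| Spread | As planned | Plus five signs | Plus one score |
|---|---|---|---|
| 0 | 76.2% | 74.8% | 76.3% |
| 0.3 | 70.7% | 74.5% | 75.7% |
| 0.5 | 63.6% | 74.9% | 75.8% |

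  If the signs carry no information, five separate terms cost about 1 point and a single score costs nothing visible. Type I error ran at 5 to 8% in all three models, so the differences between columns matter more than the levels.

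The Cox model therefore moves in the same direction as the linear model, from nil upward.

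**The case against.** The strongest reply is that this is a preference. The list was fixed in advance on clinical grounds, includes the stratification factor and an inflammatory marker, and is defensible. That stands: nothing in the article is contradicted by leaving starting status out.

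The size of the gain is also unsupported. The documents give no correlation, and below a partial correlation of about 0.2 the gain is negligible. That stands too, and is why the range starts at nil.

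Two practical objections also hold. Table 1 says only vital signs, so a room-air oxygen value at randomization is an inference. And since no criterion requires instability at entry, some patients could have a count of zero, meaning that the endpoint is already met at time zero. The simulations contain no such patients. Nor do they test whether a linear count satisfies proportional hazards, and starting status may well act mainly on the early hazard.

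A reader might infer three stronger things, none of which the documents support:

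- That none of the five signs is adjusted for. Respiratory rate and blood pressure enter partly through CURB-65.
- That the trial falls short of its stated 80% power because of this omission. The calculation compares unadjusted means and claims no benefit from covariates, so the omission takes nothing from it. The falling column in the second simulation comes from holding the conditional hazard ratio fixed while the prognostic spread grows; it does not recompute the plan's power.
- That chance imbalance in starting status biases the result. Randomization protects the comparison, and chance imbalance is already covered by the type I error rate.

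**Conclusion.** The point holds as an improvement, not as an error. The primary model has no term for status on the endpoint criteria at time zero, although vital signs are scheduled then. Three of the five criteria are wholly absent from the covariates and two are only partly represented.

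The direction of the benefit is secure if starting status is prognostic, which is plausible for a threshold endpoint. The size is assumed. On the plan's t-test inputs, with the planned covariates at correlation 0.3, the gain runs from 0 to about 9 points for partial correlations of 0 to 0.5, and exceeds 5 points only at about 0.4 or more. A Cox gain from nil to several points is a fair expectation.

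**What to change.** Before unblinding, and preferably before recruitment, add one prespecified covariate to the primary Cox model and to the adjusted linear-regression sensitivity analysis: the number of the five Textbox 2 criteria unmet at the last observation before randomization, entered as a single linear term.

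Three details should be written with it:

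- An analysis coding rule for patients without a room-air oxygen value at that observation.
- Confirmation that the baseline vital signs in Table 1 include oxygenation.
- Inclusion of the new term in the planned Schoenfeld-residual and log-log checks.

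A single count is preferable to five separate terms, given the length of the covariate list and about 100 to 124 patients.

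The cost is a few lines of analysis text and one degree of freedom. If oxygenation is among the recorded signs, no further patients, visits or measurements are needed. The hazard ratio becomes conditional on starting instability, and the report should say so.

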### Rationale for Vitamin C Supplementation

Inflammation and oxidative stress are central to the pathophysiology of CAP and its complications, including respiratory failure and sepsis-related organ dysfunction, through the excessive production of reactive oxygen species and proinflammatory cytokines, with consequent tissue injury [5-7]. Vitamin C (ascorbate) is a key antioxidant with immunomodulatory properties; however, humans cannot synthesize it endogenously and rely entirely on dietary intake [8].

Hypovitaminosis C is common in acute illness due to increased metabolic demand, reduced intake, and enhanced losses and has been associated with worse outcomes in sepsis and pneumonia [9-11]. Among hospitalized patients with CAP, our research [12] suggests that 42.6% are vitamin C deficient and these patients had 23% longer hospital length of stay (LOS; incidence rate ratio=1.23, 95% CI 1.06-1.42; *P*=.005) and 3-fold longer ICU LOS (incidence rate ratio=3.07, 95% CI 2.18-4.30; *P*<.001) after adjustment for age, comorbidities, frailty status, and pneumonia severity when compared to patients who were not deficient. There was a trend toward increased in-hospital mortality (adjusted odds ratio 4.23, 95% CI 0.58-30.48) and 30-day mortality (adjusted odds ratio 3.82, 95% CI 0.71-20.50) among patients who had vitamin C deficiency. Randomized trials evaluating vitamin C in the treatment of infections have yielded inconsistent results. While some studies suggest improvements in respiratory parameters, larger trials in patients with sepsis who are critically ill have not demonstrated a clear mortality benefit, potentially due to differences in patient populations, formulation, dosing strategy, and abrupt discontinuation of therapy [13-15]. Furthermore, evidence specific to hospitalized patients with CAP outside the ICU remains limited.

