#### Subgroup Analyses

Prespecified subgroup analyses will examine the effects of vitamin C in clinically important subgroups, including older participants (aged <65 years vs ≥65 years), participants with frailty (Clinical Frailty Scale score of 1-5 vs ≥5), participants with moderate to severe pneumonia (CURB-65 score of <2 vs ≥2), and participants with higher multimorbidity burden (Charlson Comorbidity Index of <3 vs ≥3). Separate regression models will be performed for each subgroup.

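### The primary Cox model leaves out frailty and adjusts for comorbidity through an open list of examples, giving up a modest and avoidable amount of precision

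*Protocol article*

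**What the plan says.** Primary Outcome Analysis states that the Cox model for time to clinical stabilization is "adjusted for the following prespecified baseline covariates selected a priori based on clinical relevance". The list is age, sex, CURB-65 score, baseline C-reactive protein and "key comorbidities (eg, chronic cardiovascular, respiratory, or metabolic conditions". The reason given is: "These covariates were selected to account for potential confounding effects of multimorbidity on clinical recovery". The linear-regression sensitivity analysis uses the same covariates.

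Frailty is not among them. It appears in two other places that matter here:

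- Subgroup Analyses plans a comparison for "participants with frailty (Clinical Frailty Scale score of 1-5 vs ≥5" and, separately, one for "participants with higher multimorbidity burden (Charlson Comorbidity Index of <3 vs ≥3".
- Rationale for Vitamin C Supplementation reports the team's earlier findings on vitamin C deficiency and length of stay "after adjustment for age, comorbidities, frailty status, and pneumonia severity".

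The Background section also names frailty, with age and multimorbidity, as a setting in which mortality is high.

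**The concern.** Two things stand out when these sections are read together.

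First, of the four kinds of variable in the team's earlier adjustment set (age, comorbidity, frailty, pneumonia severity), only frailty is missing from the primary model. The trial still needs the frailty score for a planned analysis. In a Cox model, leaving out a prognostic baseline variable moves the estimated hazard ratio toward 1 and costs power. This trial is sized at 80% power with no visible reserve beyond the attrition allowance.

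Second, the covariates are called prespecified, but the comorbidity part is illustrative. The number, definition and coding of its terms are not fixed. The stated aim is to handle multimorbidity, and the article already uses one defined score for that elsewhere.

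At stake is some power for the primary comparison, and a primary model that a reader could reproduce from the text.

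**Working it through.** **Inputs.** Sample Size Calculation gives a difference of 1.1 days, pooled SD 1.95, 80% power, two-sided alpha 0.05, and 102 evaluable patients (51 per group). Study Design gives 1:1 allocation. The extra share of outcome variance explained by frailty, written R² below, is not in the document and is varied.

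**Step 1: reproduce the stated sample size.** The normal formula is n per arm = 2(1.960 + 0.842)² × 1.95² / 1.1² = 2 × 7.85 × 3.8025 / 1.21 ≈ 49.3, rounded up to 50. The t-test version gives 50.3, rounded up to 51 per arm, or 102. The stated figure reproduces. It assumes no covariate adjustment, so the covariate list does not change it.

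**Step 2: value of one more prognostic covariate on the means scale.** Power = Φ(1.1 / (1.95 × √(1 − R²) × √(2/51)) − 1.960).

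- With R² = 0: 1.1 / (1.95 × 0.198) = 2.849, and Φ(0.889) = 81.3%.
- With R² = 0.10: 2.849 / √0.90 = 3.003, and Φ(1.043) = 85.1%.

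**Step 3: the same question in a Cox model.** One simulation used 51 per arm and lognormal times with mean ratio 3.6/4.7 and log-SD 0.47 (close to 1.95 / 4.15, where 4.15 is the midpoint of the two means). It compared Cox models with and without frailty, no other covariate present, over 4,000 runs. A second simulation put stand-ins for the planned covariates in the model first (102 patients, 2,000 runs, assumed inputs).

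| Extra share explained by frailty | Means-scale power | Gain (points) | Cox gain, no other covariates | Cox gain, planned covariates already in |
|---|---|---|---|---|
| 0% | 81.3% | 0 | – | about 0 |
| 2% | 82.1% | 0.8 | 1.3 | about 0 |
| 5% | 83.2% | 1.9 | 2.0 | about 2.5 |
| 10% | 85.1% | 3.8 | 4.3 | about 6 |

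At 2,000 runs a power estimate near 75% has a standard error of √(0.75 × 0.25 / 2,000) ≈ 1 point, so differences between columns of a point or two should not be read closely. No power was lost when frailty carried no information.

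**Step 4: effect on the estimate.** In a 5,000-run version of the lognormal simulation, the fitted hazard ratio without frailty was about 1.70. With frailty it was about 1.75, 1.78 and 1.81 when frailty explained 5%, 10% and 15% of log-time variance. This is the known shift between hazard ratios conditional on different covariate sets.

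**Step 5: is the score available?** Table 1 has no row for the Clinical Frailty Scale or the Charlson index. It has no row for CURB-65 either, so its silence says little. Collection is inferred from Subgroup Analyses, which cannot be carried out without both scores.

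**The case against.** **Omitting frailty is not an error.** Allocation is randomized 1:1, so leaving out a prognostic variable neither confounds the comparison nor invalidates the test. The choice of prognostic covariates is a judgment for the trial team. This stands, and it rules out any claim of bias.

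**The earlier adjusted analysis sets no precedent.** A reader might infer that the team contradicts its own model. The documents do not support that. The earlier work compared deficient with non-deficient patients on length of stay, where confounding has to be controlled. It shows that the team regards frailty as relevant to recovery, but does not oblige the trial to adjust for it. A planned subgroup analysis does not oblige it either.

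**The gain may be smaller than a model with frailty alone suggests.** Frailty overlaps with age and comorbidity. When the model already held one proxy correlated 0.6 with frailty (an assumption), the gains were 1.7, 2.9 and 4.7 points at total shares of 5%, 10% and 15%. This stands, and is why the result is stated for the extra share explained.

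**The open list alone is detail that an analysis plan can close.** A reader might infer that the primary P value is open to selection. Null simulations show what free choice could do. With a log hazard ratio of 0.2 per factor, type I error was 5.4% for one fixed set and 7.5% for the best of the 8 sets that three conditions allow (4,000 runs). A 500-run simulation with other assumptions gave 7.6% and 9.6%. Both require choosing the model after seeing unblinded results. The documents do not provide for that, and Blinding says that the statisticians stay blinded. The inflation is therefore not a predicted property of this trial.

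**Conclusion.** The point holds as a low-cost improvement to the primary model, not as a correction of an error. The plan omits a baseline variable that it treats as clinically important and must record for another analysis. It also describes its multimorbidity adjustment by example, although it names a single multimorbidity score elsewhere.

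The gain is roughly 0 to 6 points of power at 102 evaluable patients, for an extra 0 to 10% of log-time variance explained. It is near zero if frailty adds 2% or less. The result rests on that assumed share, on simulated outcome distributions, and on the inference that the Clinical Frailty Scale is recorded at baseline. The sample size does not change.

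**What to change.** Before unblinding, amend the covariate sentence in Primary Outcome Analysis in two ways:

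- Add the baseline Clinical Frailty Scale score. Enter the score itself rather than the subgroup split, which as printed places a score of 5 on both sides.
- Replace the examples with one closed, coded comorbidity term. The Charlson index is the ready choice because Subgroup Analyses already needs it; a fixed list of conditions would also do.

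The linear-regression sensitivity analysis then takes the same set without further change. The schedule or case report form should confirm that both scores are recorded at baseline.

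The cost is about one sentence and no new measurement, provided the subgroup analyses go ahead as planned. The statistical downside is one more coefficient, negligible if nearly all of the 102 evaluable patients stabilize and so supply about 100 events.

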### Blinding

Participants, treating clinicians, investigators, outcome assessors, and statisticians will remain blinded to treatment allocation. Study medications will be indistinguishable in appearance, taste, and packaging. Emergency unblinding will be permissible only when knowledge of allocation is essential for clinical management.

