#### Secondary Outcome Analysis

Hospital LOS will be analyzed similarly using *t* tests or linear regression, with Cox regression as a secondary analysis. Although LOS data are likely to be nonnormally distributed, the *t* test and linear regression models are considered robust due to the sample size (n>30 per group), which satisfies the conditions of the central limit theorem.

HRQOL at 1 and 6 months will be assessed using linear mixed-effects models to account for repeated measures, and binary outcomes (eg, ICU admission and in-hospital mortality) will be compared using logistic regression. Biomarkers will be analyzed as change from baseline with adjustment for time from randomization to follow-up sampling. Linear regression and mixed-effects models incorporating time as a covariate will be used, with sensitivity analyses restricted to samples collected within a predefined time window.

Baseline differences between groups in clinical and demographic variables will be assessed using *t* tests, Wilcoxon rank-sum tests, or chi-square or Fisher exact tests as appropriate. Missing data will be addressed using multiple imputation, and additional sensitivity analyses will be performed in subgroups, such as patients with moderate to severe pneumonia (CURB-65 score≥2).

Statistical significance for all outcomes will be determined using a 2-sided type I error rate of α=.05. All analyses will be performed using Stata (version 19.0; StataCorp).

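### The outcome's distribution cannot decide between a t test and linear regression, so covariate adjustment is left unfixed in a sensitivity analysis and in the main length-of-stay analysis (minor)

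*Protocol article*

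**What the plan says.** Primary Outcome Analysis fixes the main analysis clearly: "The primary Cox model will be adjusted for the following prespecified baseline covariates selected a priori based on clinical relevance". A restricted mean survival time analysis follows as the first sensitivity analysis. The article then adds a second, a comparison of means whose method is left to a condition: "2-sided) or linear regression depending on the distribution of the outcome", the first alternative being a t test. Adjustment is mentioned only for the second option: "The linear regression model will allow for adjustment for the same prespecified covariates, and results will be reported as mean differences with 95% CIs".

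A similar approach to LOS appears in Secondary Outcome Analysis: t tests "or linear regression, with Cox regression as a secondary analysis". For LOS the pair is therefore the main analysis. That section expects LOS to be non-normal but adds that the t "test and linear regression models are considered robust due to the sample size (n>30 per group"), citing the central limit theorem. It sets a 2-sided α of .05 for all outcomes.

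The Blinding section states: "Participants, treating clinicians, investigators, outcome assessors, and statisticians will remain blinded to treatment allocation".

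**The concern.** A selection rule should point to one analysis once its criterion has been observed. This one cannot. The t test and the linear model on treatment make the same distributional assumption, so no shape of the outcome favors one over the other. What does differ is whether baseline covariates enter. The article ties that possibility to the regression option, in permissive wording, and nowhere says whether the reported estimate will be adjusted.

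For the primary outcome this concerns a second sensitivity analysis only. For LOS, which is the subject of the second secondary hypothesis, it means that no single main test is defined. At stake are a clear statement of what will be tested and the precision available from covariates that the trial already plans to use in its Cox model.

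**Working it through.** **1. The plan's own figure.** Inputs from Sample Size Calculation: difference 1.1 days, SD 1.95, power 80%, 2-sided α .05.

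n per arm = 2 × (1.96 + 0.8416)² × (1.95/1.1)² = 2 × 7.849 × 3.143 = 49.3, so 50. With the t distribution it is 50.3, so 51 per arm and 102 in total, as the article states. The trial is thus sized on an unadjusted comparison of two means.

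**2. Are the two options distinguishable by distribution?** For the model y = b0 + b1 × treatment + error, least squares gives b1 = difference in arm means, SE = pooled SD × √(1/n1 + 1/n0), and df = n1 + n0 − 2. That is the equal-variance t test. Checked on simulated data with 62 per arm:

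| Outcome | t test | Regression on treatment |
|---|---|---|
| Normal | \|t\| = 3.7303, P = .000292 | \|t\| = 3.7303, P = .000292 |
| Lognormal | \|t\| = 2.8102, P = .005770 | \|t\| = 2.8102, P = .005770 |

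A Welch t test would respond to unequal variances, not to shape, and the article does not name it.

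**3. The two sections side by side.** One section lets the distribution choose between the methods. The other says that non-normality does not matter for either. On the article's own reasoning, the criterion is empty.

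**4. Can the choice change a result?** Null simulation, 62 per arm, 20,000 trials per row, normal outcome, seven covariates. The number of covariates and the R² are assumptions; the article gives neither.

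| R² of covariates | t test rejects | Adjusted rejects | Smaller P rejects | Verdicts differ |
|---|---|---|---|---|
| 0 | 4.8% | 4.8% | 5.9% | 2.1% |
| 0.1 | 5.1% | 5.0% | 6.8% | 3.5% |
| 0.2 | 5.1% | 5.0% | 7.3% | 4.5% |
| 0.3 | 4.8% | 4.9% | 7.5% | 5.3% |
| 0.5 | 5.1% | 4.7% | 8.4% | 6.9% |

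With lognormal outcomes the smaller-P column runs from 6.0% to 8.1%. So the choice can matter in a given trial, but either test fixed in advance holds 5%.

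**5. The rule as written.** If the choice is made by a skewness test on the outcome pooled across arms, in either direction (six covariates, R² 0.1–0.5, normal and lognormal outcomes), simulated type I error is 4.6–5.3%. The pooled shape says almost nothing about the direction or size of a chance difference between arms, so choosing on it does not select for significance.

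**6. Precision forgone.** Take 51 per arm and the planned effect. Unadjusted SE = 1.95 × √(2/51) = 0.386; 1.1/0.386 = 2.849; power = Φ(2.849 − 1.96) = 81%. With k covariates explaining R², SE is approximately 0.386 × √(1 − R²) × √(99/(99 − k)), where 99 = 102 − 3 and the last factor is the price of estimating k coefficients. For k = 6, √(99/93) = 1.032:

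| R² | SE | 1.1/SE | Power |
|---|---|---|---|
| 0 | 0.398 | 2.76 | 79% |
| 0.1 | 0.378 | 2.91 | 83% |
| 0.2 | 0.356 | 3.09 | 87% |
| 0.3 | 0.333 | 3.30 | 91% |
| 0.4 | 0.309 | 3.56 | 95% |

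With k = 7 the R² = 0.1 figure is about 82%. Adjustment breaks even at R² = 6/99, about 0.06.

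**The case against.** A reader might infer that the rule inflates type I error to 7–8%. The documents do not support that. Those figures require running both tests, seeing both P values and reporting the better one, which the rule does not allow. Statisticians are blinded to allocation, so a look at the distribution would be pooled across arms, and step 5 shows no inflation in that case. This part of the objection stands in full.

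A reader might also infer that the primary conclusion is exposed. It is not: the Cox model is fixed and adjusted, restricted mean survival time is the first sensitivity analysis, and the faulty sentence governs only the second.

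For LOS, the article does not repeat the distribution criterion and in effect argues against one. What remains there is a bare choice between two methods, which an analysis plan might settle. That weakens the LOS part but does not remove it, because the article names the pair as the main analysis and links it to the preceding section.

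Two smaller points are fair. The exact identity holds for the unadjusted, equal-variance case; adjusted regression concerns residuals, whose shape can differ from that of the raw outcome. But the article's criterion is the distribution of the outcome, not of residuals. Also, the t test is the analysis that matches the sample size calculation, which is a reason to keep it as a supportive result.

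**Conclusion.** The point holds as a minor one. The stated criterion cannot choose between the two methods, so it leaves covariate adjustment unfixed in one sensitivity analysis of the primary outcome; the same open pair leaves LOS without a single defined main test. Following the rule with blinded statisticians leaves type I error at about 5%; 7–8% is a worst case that departs from the rule.

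The practical loss is precision: about 81% power unadjusted against about 82–95% adjusted. This rests on the planned 1.1-day difference and SD of 1.95, 51 per arm, six or seven covariates and an assumed R² of 0.1–0.4. If the covariates explained almost nothing, adjustment would cost about two percentage points of power. The power figures apply to the planned stabilization difference; the article gives no separate planning figures for LOS.

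**What to change.** In Primary Outcome Analysis, delete the clause that makes the method depend on the outcome's distribution. Name one model for the additional sensitivity analysis: linear regression adjusted for the covariates of the primary Cox model, including CURB-65 severity, since randomization is stratified by pneumonia severity. In Secondary Outcome Analysis, name the same model as the main LOS analysis and keep Cox regression as secondary. Report the unadjusted t test for both as supportive only, with no claim attached. List the comorbidity covariates, which are now given only as examples, so that the same covariates means one fixed set. If skewness is a concern, specify robust or bootstrap standard errors, which respond to it.

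The cost is about one sentence in each of two paragraphs, with no change to sample size, data collection or conduct. Recruitment is scheduled to start in 2026 and analysis follows completion of follow-up, so the choice can be fixed before any outcome data are examined.
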